## Statistical considerations

### Sample size calculations

The required sample size is calculated based on the primary outcome, which is a fall within 30 days of surgery. Appropriate logistic regression models contain at least 10 ‘events’ per predictor variable.^20^ Since our prespecified model for postoperative falls includes 13 dependent variables (see the Analysis section), a sample with at least 130 events is required. In our population, preliminary work shows that ∼10% of patients report falling in the month following surgery. Thus, the minimum sample size needed for this study is 1300 patients.

Currently, our database contains over 9000 complete records (ie, baseline and 30-day survey) after the 16 January 2014 start date. To meet statistical assumptions of independent observations, we estimate that ∼600 records from patients with at least one previous entry in the data set will be excluded. We estimate that an additional 600 records will be excluded due to inappropriate time intervals (baseline survey to surgery <0 or >59 days; surgery to 30-day survey <20 or >120 days; or surgery to 1-year survey <275 or >455 days). Thus, our final sample size will be ∼7800.

Within this final sample, two versions of the 30-day (V.2 and V.3) and 1-year surveys (V.1 and V.2) were administered. Only V.3 of the 30-day survey and V.2 of the 1-year survey contain a validated falls question, as recommended by the Prevention of Falls Network Europe consensus group.^21^ The difference in question phrasing caused statistically significant differences in the percentage of patients reporting postoperative falls (5.5% vs 10% at 30 days and 18% vs 28% at 1-year, p<0.001). Out of the available records, about 20% (1500) completed V.3 of the 30-day survey, which is more than the 1300 required for the primary outcome. Thus, to maximise outcome validity, only these versions will be used for postoperative falls. In contrast, the readmission question contained only minor differences (‘Were you readmitted to the hospital?’ for V.2 vs ‘Check all that apply […] admitted to a hospital’ for V.3). The percentage reporting readmission was similar between surveys (5.2% vs 5.7%, p=0.416), so the results from both versions will be combined. The remaining outcomes were identical and will use all available data from both versions of the 30-day and 1-year surveys.

Comparing patients who reported falling preoperatively with those who did not, a sample size of 1500 has 80% power to detect a 58% increase in postoperative falls within 30 days. The estimated percentage of patients who experience functional decline in the month following surgery is 20%.^22^ Our own data suggest that the SD for quality of life is 11, 28% of patients experience in-hospital complications, and 5.5% of patients are readmitted within 30 days. Thus, a sample size of 7800 patients has 80% power to detect a 15% increase in functional decline after surgery, a 0.8 point difference in physical and mental qualities of life, a 12% increase in in-hospital complications, and a 34% increase in 30-day readmission. All of the above calculations used two tails, α=0.05 and a baseline fall proportion of 26%.^17^

The minimum important difference will be a 20% difference in proportions or ORs.^23^ From the calculations above, the detectable effect sizes for falls and readmission are larger than this prespecified threshold. However, the results of interest are the ORs from regression models rather than crude bivariate analysis. For quality of life estimates, the minimum important difference will be five points.^24^
^25^

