Presence or absence of at least one fall in the 30 days (primary outcome) and 1 year following surgery:
Physical activity level (<4 vs >4 metabolic equivalents (METs));Baseline altered elimination (bowel or bladder);Baseline mobility abnormality;Dizziness/vertigo;Depression.▸Barthel Index that is worse than baseline, at 30 days and 1 year after surgery:
Baseline Barthel Index score;Neurological impairment;Mood disorder (depression or anxiety);Smoking status.▸Physical quality of life score, at 30 days and 1 year after surgery:
Baseline physical quality of life score;Preoperative physical activity level (<4 vs >4 METs);Chronic pain;Mood disorder (depression or anxiety);Smoking status.▸Mental quality of life score, at 30 days and 1 year after surgery:
Baseline mental quality of life score;Chronic pain;Mood disorder (depression or anxiety).▸Presence or absence of any complication that occurred in the hospital, as reported in the 30-day survey:
Smoking status.▸Presence or absence of readmission at 30 days, as reported in the 30-day survey:
In-hospital complications (30-day survey);Incontinence.

After running each model, we will substitute the number of falls (0, 1, 2, 3+) explanatory variable for the falls and fall injuries composite scale^27^ to evaluate which scale better predicts outcomes. Since we test multiple hypotheses, the threshold for significance will be α=0.01. We will report results using ORs and 99% CIs, along with variance estimates for regression parameters.

Using SAS/STAT software, V.9.4 (SAS Institute, Cary, North Carolina, USA), [name] will perform all analyses. Analysis will begin only after acceptance of this protocol for publication. This approach reassures readers that key analyses were truly prespecified rather than post hoc. If the authors decide to perform post hoc analyses, these will be described as such and will be performed for the purpose of further hypothesis generation.

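### Pooling of the two readmission questions rests partly on a non-significant test that cannot establish similarity, and the readmission model has no survey-version term (minor, secondary outcome)

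*Protocol article*

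**What the plan says.** The 30-day survey was given in two versions. In Sample size calculations the article states that "the readmission question contained only minor differences". V.2 asks directly whether the patient was readmitted, while V.3 offers a tick-list entry, "Check all that apply […] admitted to a hospital". It continues: "The percentage reporting readmission was similar between surveys (5.2% vs 5.7%, p=0.416), so the results from both versions will be combined". The Limitations section repeats that the readmission items are similar enough to combine.

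The same section gives the sizes: "our final sample size will be ∼7800", of whom "about 20% (1500) completed V.3 of the 30-day survey". It also sets a threshold for effects of interest: "The minimum important difference will be a 20% difference in proportions or ORs".

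In Analysis, the outcome is "Presence or absence of readmission at 30 days, as reported in the 30-day survey". The model enters by force eight common variables (age, sex, race, BMI, preoperative falls, Charlson index, ASA status, procedural cardiac risk) plus in-hospital complications and incontinence. Survey version is not among them.

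**The concern.** A non-significant difference is read as evidence that two items give the same answer. That reading needs a test able to detect a difference that matters, or a confidence interval narrow enough to rule one out. The article gives neither, and no margin is stated.

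Readmission at 30 days is a named secondary outcome, intended to replicate a result from a previously published study (Aim 2c). If the two versions produce different reporting rates, and if fallers are unevenly spread across them, an unmodelled version effect would enter the falls OR. The authors had reason to be alert to wording: in the same survey, a change of phrasing took reported 30-day falls from 5.5% to 10%.

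**Working it through.** **Inputs.** All come from Sample size calculations unless marked as assumed.
- Total about 7800; V.3 about 1500; V.2 by subtraction 7800 − 1500 = 6300.
- Readmission 5.2% (V.2) and 5.7% (V.3).
- Yardstick of 20% relative: 5.2% × 1.2 = 6.24%.
- Two-sided α=0.05, the level used for the article's own power figures. It is assumed for the version test, whose level is not stated.

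**1. Reproducing the stated p-value.** Uncorrected chi-square on whole-number counts (328/6300 and 86/1500): difference 0.00527, z = 0.82, p = 0.413. An exact 80/20 split (6240/1560) gives 0.419. Rounding in the two percentages alone allows about 0.34 to 0.54. The stated 0.416 is reproduced, which supports the assumed group sizes.

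**2. Power for a 20% relative difference.**
- Difference d = 0.0624 − 0.052 = 0.0104.
- Pooled rate = (327.6 + 93.6)/7800 = 0.0540.
- SE under no difference = √[0.0540 × 0.9460 × (1/6300 + 1/1500)] = 0.00649.
- SE under the alternative = √[0.052 × 0.948/6300 + 0.0624 × 0.9376/1500] = 0.00684.
- Power = Φ[(0.0104 − 1.96 × 0.00649)/0.00684] = Φ(−0.34) = 36.7%, so the chance of missing it is 63.3%.

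The miss chance is 54% to 63% over base rates of 5.2% to 5.7%, both directions, and splits including 7200/1800 (80/20 of the 9000 records before exclusions). It is 67% if the 20% is taken on the OR scale, and 76% to 84% at α=0.01. At 6300/1500, 80% power is reached at a ratio of about 1.36.

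**3. What the data exclude.**
- Ratio = 5.7/5.2 = 1.096; log ratio 0.0918.
- SE = √[0.948/327.6 + 0.943/85.5] = 0.118.
- 95% CI = exp(0.0918 ± 1.96 × 0.118) = 0.87 to 1.38.

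A 20% difference lies inside this interval. The falls shift, 10/5.5 = 1.82, lies well outside it, and the test's power for a ratio that large exceeds 99.9%.

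**4. Consequence for the falls–readmission OR.**
- If version is unrelated to preoperative falls, a true OR of 1.34 stays 1.34 after pooling, even with a version effect of 20% to 40% on the odds.
- Assume a strong imbalance, with V.3 used by 25% of fallers and 17% of non-fallers, a version effect of 1.2 on the odds, and no true falls effect. The V.3 rate is then 6.18%. Non-fallers: 0.83 × 5.2% + 0.17 × 6.18% = 5.37%. Fallers: 0.75 × 5.2% + 0.25 × 6.18% = 5.44%. The OR is 1.015.
- With a version effect of 1.38, the OR is 1.028.

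**5. What a version covariate can and cannot do.** Take an assumed example: true readmission 5%, falls risk ratio 1.5, 26% fallers. An item with sensitivity 0.95 and specificity 0.996 gives 5.1% overall and a falls OR of 1.49. An item with sensitivity 0.60 and specificity 0.974 gives 5.5% and 1.26. With the first item on 6300 records and the second on 1500, the pooled OR is 1.44 with the covariate and 1.44 without it, and the version term itself is 1.07 (p=0.59). Power to tell 1.49 from 1.26 by version is about 9% at α=0.05 and 2.5% at α=0.01. The V.3-only OR of 1.26 would have a 99% CI of about 0.67 to 2.39.

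**The case against.** **The p-value is not the only ground.** The authors also judged the wording differences minor and noted that the percentages lie half a point apart. This stands. The text nevertheless presents the pooling as following from the comparison of percentages and its p-value.

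**The 20% is not an equivalence margin.** It is set for effects on outcomes, and a 20% difference between versions is not a 20% error in the falls OR. This stands, so 37% power describes how little the test can show and does not breach a stated criterion.

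**The falls item cuts the other way.** The same kind of check did catch the falls wording, and the authors excluded the non-validated version. For readmission, a shift of that size is ruled out. This stands.

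**Stronger readings that the documents do not support.**
- A reader might infer that pooling materially biases the falls OR. Step 4 shows a shift of 2% to 3% at most under a strong assumed imbalance, and the article does not report that fallers are unevenly spread across versions.
- A reader might infer that the two items differ in accuracy and that a version term would correct this. The sensitivities and specificities in step 5 are invented, and the covariate leaves that example unchanged.
- A reader might infer that an unticked V.3 box cannot be told from a skipped item. That depends on the V.3 form, which is in the supplement and not shown; the quoted item is itself abridged.

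**Disclosure.** The Limitations section reports the two versions and their combination, and says that readmission does not come from a standardised tool. That is fair, but it repeats the claim of similarity and does not support it further.

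**Conclusion.** The concern holds in a limited form. Non-significance at p=0.416 does not show that the two readmission items report at the same rate: the data are compatible with a V.3/V.2 ratio from about 0.87 to 1.38. The fixed covariate list contains nothing to absorb such a difference. Pooling itself remains reasonable, and a gross wording effect of the kind seen for falls is excluded.

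This rests on V.2 n of about 6300 by subtraction and on two-sided α=0.05 for the version test. The size of the confounding also rests on the assumed 25% versus 17% imbalance. The point is minor: a flaw of reasoning on a secondary outcome, with a small expected effect on the estimate.

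**What to change.** 1. Keep both versions combined. In Sample size calculations, replace p=0.416 as the justification with the between-version ratio and its CI (about 1.10, 0.87 to 1.38), and say that equivalence is not established. Make the matching change in Limitations.
2. Add survey version (V.2/V.3) to the prespecified readmission model, so that a version difference in reporting rate cannot confound the falls OR.
3. Show the falls–readmission OR by version with CIs, labelled as descriptive. V.3 has only about 0.057 × 1500 ≈ 85 events and cannot reliably detect heterogeneity, so agreement between versions should not be read as proof of equal accuracy.

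The cost is one parameter in a model with about 410 to 430 events (328 + 86 = 414 from the version percentages; 0.055 × 7800 = 429 from the overall rate) and one small table. Version must already be identifiable for each record, because the falls analysis selects on it. No new data are needed.

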**Methods and analysis:**

To achieve these goals, we study adult patients who underwent elective surgery at our academic medical centre and were recruited to participate in a prospective, survey-based cohort study called Systematic Assessment and Targeted Improvement of Services Following Yearlong Surgical Outcomes Surveys (SATISFY-SOS) (NCT02032030). Patients who reported falling in the 6 months prior to surgery will be considered ‘exposed.’ The primary outcome of interest is postoperative falls within 30 days of surgery. Secondary outcomes include postoperative functional dependence, quality of life (both physical and mental), in-hospital complications and readmission. Regression models will permit controlling for important confounders.

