Aim 2 explores whether a preoperative history of falls serves as a useful tool for predicting surgical outcomes. First, we will calculate a crude dose–response relationship between the number of falls at baseline (0, 1, 2, 3+) and each outcome (postoperative falls, postoperative functional dependence, postoperative quality of life, in-hospital complications and 30-day readmission). For comparison, we will also calculate the crude dose–response relationship for a falls and injuries composite scale.^27^ We will examine the bivariate relationship between preoperative falls and each complication subcategory (heart/stroke, lung, blood clots, kidney/intestine, nerve injury, infection, delirium or other) using χ^2^ tests for the purpose of hypothesis generation.

To assess the relationship after controlling for important confounders, we will use logistic regression (categorical outcomes) and linear regression (continuous outcomes). Specifically, we will use forced entry of all prespecified variables. We will check all models for linearity of logit, multicollinearity, influential cases, conformity to linear gradients and goodness of fit. Since the number of possible interaction terms is large (between 45 and 91 per model), including all of them creates an unacceptably large risk of type I error. Therefore, our statistical consultant ([name]) recommended selecting only 10% of the most clinically relevant interaction terms. Using a combination of prior research and clinical judgement, two investigators ([name] and [name]) selected the 10% most clinically relevant interaction terms for each model. The online supplementary material contains these prespecified interaction terms. Non-significant interaction terms (p>0.01) will be removed from the model.

10.1136/bmjopen-2016-011570.supp8Supplementary data

Each model will include the following demographic and explanatory variables: age, sex, race (white vs non-white), BMI, preoperative falls history (0, 1, 2, 3+), Charlson Comorbidity Index (≥3 vs <3), American Society of Anesthesiology (ASA) physical status (≥3 vs <3) and procedural cardiac risk. On the basis of a careful literature search of each outcome variable (see the Literature search and review section), we selected confounding variables that are both routinely collected and known at the time of surgery planning. Outcome variables and their corresponding outcome-specific confounders are listed below.

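### The 80% power statements use α=0.05, but the analysis tests at α=0.01; at the stated effects power is about 60%

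*Protocol article*

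**What the plan says.** The Sample size calculations section gives effects detectable with 80% power. They are a 58% increase in 30-day falls with 1500 patients and, with 7800 patients, a 15% increase in functional decline, 0.8 points in quality of life, a 12% increase in complications and a 34% increase in readmission. The contrast has two groups: "Comparing patients who reported falling preoperatively with those who did not". The basis is stated once for all five: "All of the above calculations used two tails, α=0.05 and a baseline fall proportion of 26" per cent.

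The Analysis section sets a stricter level: "Since we test multiple hypotheses, the threshold for significance will be α=0.01". It continues: "We will report results using ORs and 99% CIs, along with variance estimates for regression parameters". Nothing there exempts the primary outcome.

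The form of the exposure also changes. The abstract makes it binary: "Patients who reported falling in the 6 months prior to surgery will be considered ‘exposed". The Analysis section enters "preoperative falls history (0, 1, 2, 3" or more) in every model.

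The minimum important difference is 20% in proportions or ORs, and five points for quality of life. The protocol concedes that the detectable effects for falls and readmission are larger than 20%, and adds: "However, the results of interest are the ORs from regression models rather than crude bivariate analysis".

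**The concern.** A power statement describes the test that will be run. Here the power is computed at one significance level and the results are judged at another, and no passage reconciles the two. A reader who meets a non-significant result on postoperative falls would set it against a claimed 80% power for a 58% increase, which a test at α=0.01 does not have. The risk is that imprecision is read as absence of effect, above all for the primary outcome, which rests on about 1500 patients.

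The powered contrast (any fall against none) also differs from the exposure that the models contain (0, 1, 2, 3+). No single test of that exposure is named as the one to which the power statement applies.

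**Working it through.** **Inputs (all from Sample size calculations unless noted).** Exposed share 26%. Overall risks: 30-day falls about 10%, functional decline 20%, complications 28%, readmission 5.5%. Quality-of-life SD 11. N = 1500 for falls and 7800 for the rest. α = 0.05 there and 0.01 in Analysis.

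**Method.** Two-sided, pooled two-proportion z-test with group sizes 0.74N and 0.26N. The stated risk p is taken as the overall risk, so for relative risk RR:

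- p0 = p / (0.74 + 0.26·RR), p1 = RR·p0, d = p1 − p0
- s0 = √[p(1−p)(1/n0 + 1/n1)], s1 = √[p0(1−p0)/n0 + p1(1−p1)/n1]
- power = Φ[(d − z·s0)/s1], with z = 1.960 at α=0.05 and 2.576 at α=0.01

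**Primary outcome in full.** RR = 1.58 gives p0 = 0.10/(0.74 + 0.26×1.58) = 0.0869, p1 = 0.1373 and d = 0.0504. With n0 = 1110 and n1 = 390, s0 = 0.01766 and s1 = 0.01937.

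- α=0.05: (0.0504 − 1.960×0.01766)/0.01937 = 0.815, power 79.2%. The protocol's 80% reproduces.
- α=0.01: (0.0504 − 2.576×0.01766)/0.01937 = 0.254, power 60.0%.

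**Quality of life.** SE = 11·√(1/5772 + 1/2028) = 0.284. For 0.8 points, power is Φ(0.8/0.284 − 1.960) = 80.4% at α=0.05 and Φ(0.8/0.284 − 2.576) = 59.5% at α=0.01. The difference detectable with 80% power is (1.960 + 0.842)×0.284 = 0.80 points, or (2.576 + 0.842)×0.284 = 0.97 points.

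**All five outcomes.**

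| Outcome | Stated effect | Power, α=0.05 | Power, α=0.01 | Detectable at 80%, α=0.05 | Detectable at 80%, α=0.01 |
|---|---|---|---|---|---|
| 30-day falls | 58% | 79.2% | 60.0% | 58.7% | 74.0% |
| Functional decline | 15% | 79.3% | 58.5% | 15.1% | 18.6% |
| Quality of life | 0.8 points | 80.4% | 59.5% | 0.80 | 0.97 |
| Complications | 12% | 79.9% | 59.2% | 12.0% | 14.8% |
| Readmission | 34% | 81.6% | 62.6% | 33.2% | 41.3% |

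As a general check, a test with exactly 80% power at α=0.05 has Φ(1.960 + 0.842 − 2.576) = 58.9% at α=0.01. For falls, 80% power at the stated 58% increase would need about 2255 patients at α=0.01, against about 1500.

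**Against the protocol's threshold.** Power for a 20% relative increase in proportions (RR = 1.20):

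| Outcome | α=0.05 | α=0.01 |
|---|---|---|
| 30-day falls | 19.8% | 7.5% |
| Functional decline | 95.2% | 85.8% |
| Complications | 99.5% | 97.5% |
| Readmission | 43.0% | 22.2% |

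Power for five quality-of-life points is essentially 100% at either level.

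**Sensitivity to the reading of the risks.** If the stated risks are those of the unexposed group, power at α=0.05 is 84.9% for falls and 84.7% for readmission, which matches the protocol less well. At α=0.01 these become 68.0% and 67.3%.

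**Exposure coding, kept apart from the above.** The protocol gives no 0/1/2/3+ distribution and does not state categorical or linear entry. Under assumed splits of the 26% (for example 14/6/6), for the primary outcome at α=0.01:

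- a 3-df test with equal risk at every fall count gives about 41–43%;
- a 1-df trend test gives about 43–48% for that same flat effect;
- a 1-df trend test gives about 72–77% for a truly linear gradient.

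The range of about 41% to 77% lies on both sides of 60%.

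**The case against.** The strongest reply is that power did not set the sample size. The required 1300 comes from ten events per model variable, and the 1500 and 7800 are what an existing database supplies. Correcting α therefore changes no enrolment and no analysis, and the 99% CIs will show the imprecision. That stands and limits the consequence, but the stated 80% is still not the power of the planned tests.

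The protocol also already discloses that falls and readmission exceed its 20% threshold. That stands too. What is undisclosed is that the gap is wider at the α actually used.

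Four stronger readings are tempting and are not supported:

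- **That the four-level exposure helps to produce the 60%.** It does not; the 60% comes from α alone with a binary exposure. The coding could lower or raise power. The count of 13 model variables treats falls as one term, which is compatible with a single ordinal term.
- **That every outcome is now underpowered against the threshold.** On the OR scale the detectable ORs at α=0.01 are 1.87 (falls), 1.24 (functional decline), 1.21 (complications) and 1.44 (readmission), all above 1.20. But the protocol allows proportions as well, and on that scale 18.6% and 14.8% stay below 20%.
- **That the protocol claims regression cures the shortfall.** Its sentence says only that crude comparisons are not the results of interest. Moving to adjusted ORs does not by itself make smaller effects detectable, but the text does not say that it does.
- **That 0.97 points is a firm figure for quality of life.** Those models are linear and include the baseline score, which can reduce the residual SD. The crude figure may overstate the detectable difference.

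**Conclusion.** Wrong as written. The arithmetic at α=0.05 is sound, but it is not the α of the analysis. At α=0.01 the stated effects have about 60% power (58.5% to 62.6%), and the effects detectable with 80% power are about a fifth to a quarter larger than stated. The practical shortfall concerns the primary outcome and readmission. Functional decline, complications and quality of life remain adequately powered against the protocol's own thresholds, with 20% read as a relative increase in proportions.

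This rests on crude two-group comparisons, a 26:74 split and the stated risks taken as overall risks, a reading supported by the close match at α=0.05. The difference between the powered exposure and the modelled one is a real second inconsistency. Its effect on power cannot be fixed from the document and forms no part of the 60%.

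**What to change.** 1. Restate all five detectable effects at α=0.01: about 74%, 18.6%, 0.97 points, 14.8% and 41%. Alternatively, state explicitly that the primary outcome is tested at 0.05. The 58% figure could then stay, with a matching interval level for that outcome, and the other four would still be restated.
2. Name the single primary test of preoperative falls to which the power statement applies: any fall against none, or one trend or global test across 0, 1, 2, 3+. If it is not the any-versus-none contrast, recompute power for it with the observed distribution of fall counts.
3. State that a non-significant result whose 99% CI includes both 1 and the minimum important OR (1.20, if the 20% is applied to ORs) will be reported as inconclusive, not as no effect. The CI must include 1 as well; otherwise a clearly significant OR with a wide interval would be called inconclusive.

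The cost is text only, with no new data. The downside is that the stated detectable effects become less favourable.

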## Background

### Literature search and review

In preparation for this study, a systemised review of the literature was performed on preoperative and postoperative falls.^3^ This review showed that a limited number of studies on postoperative falls have been conducted, and the few that have been performed mostly study orthopaedic and elderly populations. While one study characterised postoperative falls in all surgery types, it was limited by its retrospective design, inpatient time period and exclusively male population.^4^ Another study suggested that most postoperative falls may be surgery related, especially in the first weeks following surgery. However, it only tracked falls that resulted in hospital care, and its follow-up period was limited to 90 days.^5^

Regarding the second aim of predicting postoperative outcomes, our systemised review identified just one paper that studied the association between preoperative falls and postoperative complications and readmission.^6^ However, the sample size was small (235), and the population included only men over 65 undergoing cardiac or colorectal surgery at a Veterans Affairs hospital. Using Medical Subject Heading (MeSH) terms of ‘accidental falls’, ‘postoperative period’ and each outcome, a thorough PubMed search was also performed to identify other relevant papers linking falls, surgery and each outcome of interest. This search showed that in non-surgical patients, falls are associated with greater functional dependence.^7^
^8^ In addition, preoperative frailty and geriatric syndromes, which are linked to falls, are associated with postoperative complications^9–14^ and readmission.^15^
^16^ Together, these findings suggest that falls before surgery may presage worse surgical outcomes. However, replication in a larger study is needed.

An additional literature search was performed to identify important confounders for each proposed outcome. Searches consisted of PubMed MeSH for each outcome, along with the MeSH, ‘Risk Factors’, in order to generate a thorough search. Variables that were strongly associated with the outcomes and that would be available to clinicians during preoperative assessment were included as confounders. In addition to confounders from the literature, our previous study on preoperative falls^17^ guided selection of confounders for postoperative falls. That is, variables with ORs of 1.5 or higher were included.

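### The 80% power for 30-day falls belongs to a crude two-group comparison; pointing to the adjusted ORs does not answer the admitted failure to reach the 20% minimum important difference

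*Protocol article*

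**What the plan says.** All of this is in the Protocol article.

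- *Sample size calculations*, basis of the power figure: "Comparing patients who reported falling preoperatively with those who did not", the plan states that "a sample size of 1500 has 80% power to detect a 58% increase in postoperative falls within 30 days". The settings are given as "All of the above calculations used two tails, α=0.05 and a baseline fall proportion of 26" per cent.
- *Sample size calculations*, inputs for falls: about "10% of patients report falling in the month following surgery". Only version 3 of the 30-day survey counts for this outcome: "about 20% (1500) completed V.3 of the 30-day survey, which is more than the 1300 required for the primary outcome". The 1300 comes from ten events per predictor, a rule that contains no effect size and no power.
- *Sample size calculations*, threshold: the minimum important difference is 20%, for proportions or ORs. The plan acknowledges that the detectable effects for falls (58%) and readmission (34%) are larger. The next sentence is "However, the results of interest are the ORs from regression models rather than crude bivariate analysis".
- *Analysis*: "To assess the relationship after controlling for important confounders, we will use logistic regression (categorical outcomes) and linear regression (continuous outcomes"), with all prespecified covariates forced in. Significance is judged at α=0.01, with 99% CIs.
- *Literature search and review*: the authors' earlier study of preoperative falls guided the choice of confounders for postoperative falls: "That is, variables with ORs of 1.5 or higher were included".

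**The concern.** The plan attaches a power figure to the primary outcome, but the figure belongs to a different analysis from the one that will be reported. The covariates were chosen partly for their association with preoperative falls, which is the exposure, so the adjusted OR should be estimated somewhat less precisely than the crude one.

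The reply to the admitted shortfall then leads nowhere. It directs the reader to the regression ORs, for which no power is given. Those ORs are held to the same 20% threshold, and nothing suggests that the regression would do better. At stake is how the primary result will be read. Someone who relies on the 80% may take a non-significant adjusted OR as evidence against an effect, although the study has little chance of detecting the difference that it calls important.

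**Working it through.** **Inputs.** From *Sample size calculations*: n=1500; 26% exposed, so 390 exposed and 1110 unexposed; 30-day fall rate 10%; two-sided α=0.05. The plan does not say whether 10% is the rate overall or in the unexposed, so both are shown. The exposure is kept binary, as in the plan's own calculation.

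**1. Reproducing the plan's figure (crude test, 10% overall).**
- Unexposed rate p₀ = 0.10/(0.74 + 0.26×1.58) = 0.0869. Exposed rate p₁ = 1.58×0.0869 = 0.1373. Difference 0.0504.
- SE under the null = √[0.10×0.90×(1/1110 + 1/390)] = 0.01766.
- SE under the alternative = √[p₀(1−p₀)/1110 + p₁(1−p₁)/390] = 0.01937.
- Power = Φ[(0.0504 − 1.96×0.01766)/0.01937] = Φ(0.815) = 79%.

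With 10% in the unexposed (10% v 15.8%), the same formula gives 85%. If 58% is read as an increase in the odds, it gives 74%, so the printed figure is a relative increase in proportions. The crude method with overall rates also returns the plan's other detectable effects: 15.1% for functional decline (stated 15%), 12.0% for complications (12%), 33.2% for readmission (34%) and 0.80 points for quality of life (0.8).

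**2. The same effect as an OR.** (0.1373/0.8627)/(0.0869/0.9131) = 1.67, or 1.69 with 10% in the unexposed. On the OR scale the effect is further from 1.20 than 58% suggests.

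**3. Allowing for adjustment.** Replace n by n(1−R²), where R² is the share of exposure variance explained by the other covariates. R² is not in the document; 0.05 to 0.20 is an assumption. The effect is held at a 58% increase and α at 0.05.

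| R² | Power, 10% overall | Power, 10% unexposed | OR detectable with 80% power (unexposed / overall) |
|---|---|---|---|
| 0 | 79% | 85% | 1.64 / 1.68 |
| 0.05 | 77% | 83% | 1.66 / 1.70 |
| 0.10 | 75% | 81% | 1.68 / 1.73 |
| 0.20 | 71% | 77% | 1.72 / 1.78 |

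**4. Power at the 20% threshold, crude test, α=0.05, stated rate taken as the unexposed rate.**
- Falls, n=1500: 21% for a 20% increase in the proportion, 17% for OR 1.20.
- Readmission, n=7800, 5.5%: 45% and 40%.
- For falls, 80% power would need about 9,800 patients (proportion) or 12,500 (OR 1.20). That is 9,800/1,500 ≈ 6.5 and 12,500/1,500 ≈ 8.3 times the available number.

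Taking the stated rates as overall rates lowers these powers by at most about two points.

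**5. At the α of the analysis.** With α=0.01 the crude power for a 58% increase is 60–68%. The detectable OR is 1.80–1.87 before adjustment and, by the formula in step 3, 1.91–2.00 at R²=0.20.

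**The case against.** The best defence is that the plan hides nothing. It says which groups are compared, admits that two outcomes miss the threshold, and separates the crude figures from the regression. The sentence with "However" can be read as a caveat that the crude figures do not describe the main analysis. Power did not set the sample size either: 1300 comes from the events-per-predictor rule, and 1500 is the number of version 3 respondents already in hand. The plan never makes 20% a power target. Finally, the planned 99% CIs will show any imprecision.

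Most of this stands, and it limits the point. The disclosure is real, and no printed number is wrong. But if the sentence is a caveat, the figure that it calls for is absent. If it is a reply to the shortfall, it is not an answer. On either reading the sentence needs replacing.

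Two stronger readings are tempting and are not supported:

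- *That adjustment would sharply cut the power.* A reader might infer this by treating part of the crude 58% as confounding. That gives lower power because the true adjusted effect is assumed smaller, which is not an error in a statement about detectable effect. It also needs covariate prevalences and covariate–outcome ORs that the document does not give. At a fixed adjusted effect the loss is what step 3 shows. With 10% in the unexposed, power is still 81% at R²=0.10.
- *That the plan claims its model can resolve a 20% effect, or will read non-significance as no effect.* It says neither.

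**Conclusion.** The point holds as a correction to how the primary analysis is described. The 80% is a property of a crude test at α=0.05. Adjustment makes the detectable OR no smaller and probably somewhat larger: from about 1.64–1.68 to 1.72–1.78 if R² is 0.20. That part is modest and rests on the assumed R² and on which group the 10% describes.

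The shortfall against the threshold needs no assumption about confounding: 17–21% power for falls and 40–45% for readmission under the plan's own crude method. Functional decline and complications are not affected in this way, since their crude detectable increases (15% and 12%) lie below 20% at α=0.05. The change should be made, but it does not invalidate the design.

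**What to change.** In *Sample size calculations*, replace the sentence beginning "However" with three statements:

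1. The detectable effects are for crude comparisons.
2. The detectable adjusted OR is no smaller and probably somewhat larger.
3. The study is not powered to detect the 20% minimum important difference for falls or readmission, with the power at that threshold printed for both.

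Add the detectable adjusted OR for falls over a stated range of R², at the α used in the analysis (0.01). R² can be estimated by regressing preoperative falls on the other model covariates in the baseline data already held; no outcome data are needed. State whether 10% is the overall rate or the rate in the unexposed.

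No separate rule for reading non-significant results is required, since ORs with 99% CIs are already planned. The cost is one short calculation, a few sentences and a less favourable stated figure. No patients are added and the analysis itself does not change.
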